- 19) Urinary tract infection, symptomatic candidiasis, or symptomatic bacterial vaginosis within 14 days of enrollment, or currently residual symptoms thereof

*Note: women with these infections at screening can be enrolled after treatment and resolution of the infection.*

- 20) Antibiotic or antifungal therapy (vaginal or systemic) within 7 days of enrollment
- 21) Use of systemic immunomodulatory medications within 4 weeks of enrollment
- 22) Menses or other vaginal bleeding at the time of enrollment\* or expecting menses in the 10 days after enrollment (Segment A participants) or 16 days after enrollment (for Segment B participants)

*\*Note: for women with monthly cycles, every attempt will be made to enroll these participants in the first half of their menstrual cycle. Women who have vaginal bleeding at the scheduled Enrollment Visit may return at a different date to be re-examined and*

*possibly enrolled provided they are still within the screening window and meet all criteria.*

- 23) Lack of stable living conditions to allow reliable room temperature storage of study product (Segment B participants only)
- 24) At enrollment has any of the following laboratory abnormalities per the *Division of AIDS (DAIDS) Table for Grading the Severity of Adult and Pediatric Adverse Events, Version 2.0, Nov 2014* (Reference 39):
- Grade 1 or higher AST or ALT
  - Grade 1 or higher creatinine
  - Grade 2 or higher hemoglobin
  - Grade 1 or higher platelets

*Note: otherwise eligible participants with an exclusionary test may be re-tested once during the screening process.*

- 25) As determined by the Principal Investigator (PI), any subject who has any significant uncontrolled active or chronic cardiovascular, renal, liver, hematologic, neurologic, gastrointestinal, psychiatric, endocrine, respiratory, immunologic disorder or infectious disease, anticoagulation with warfarin or heparin; or any other condition that, in the opinion of the Investigator, would preclude provision of consent, make participation in the study unsafe, complicate interpretation of study outcome data, or otherwise interfere with achieving the study objectives.

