The PI/designee will grade the severity of each AE and the relationship of the AE to study product:

- AE severity will be graded per the Division of AIDS (DAIDS) Table for Grading the Severity of Adult and Pediatric Adverse Events, Version 2.0. [November 2014], and the Female Genital Grading Table for Use in Microbicide Studies (Addendum 1 to the DAIDS Table for Grading Adult and Pediatric Adverse Events, Version 1.0, November 2007 [Clarification dated August 2009]), except that asymptomatic BV will not be considered an AE. AEs not included in the Female Genital Grading Table for Use in Microbicide Studies mentioned above will be graded by the Division of AIDS (DAIDS) Table for Grading the Severity of Adult and Pediatric Adverse Events, Version 2.0. [November 2014]. In cases where a genital AE is covered in both tables, the Female Genital Grading Table for Use in Microbicide Studies will be the grading scale utilized.
- The relationship of all AEs reported on CRFs will be assessed based on the Manual for Expedited Reporting of Adverse Events to DAIDS, and the clinical judgment of the PI/designee. The study products that must be considered when AE relationships are assigned are MB66 film and placebo film.

The DAIDS Table for Grading Adult and Pediatric Adverse Events, the Female Genital Grading Table for Use in Microbicide Studies, and Version 2.0 of the Manual for Expedited Reporting of Adverse Events to DAIDS are available on the DAIDS Regulatory Support Center (RSC) web site: <http://rsc.tech-res.com/>.

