### Nugent score

The morphotypes of vaginal bacteria will be assessed using Nugent scoring of Gram stained vaginal smears. The Nugent score is graded 1 to 10 as follows:

- 1) Normal, 0-3
- 2) Intermediate, 4-6
- 3) Bacterial Vaginosis, 7-10

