##### Cervicovaginal microbial environment

Vaginal pH: Vaginal pH levels will be compared between groups using two-sample t-tests. Pre- to post-exposure shifts will be analyzed with a longitudinal mixed model.

Nugent score: Differences in the categorized Nugent score at each visit and between the MB66 and placebo arms will be evaluated using chi-square tests, while McNemar's tests will be used to evaluate pre- to post-exposure shifts between normal (score 0-3) and abnormal (score 4-10) vaginal microflora within each treatment arm and from baseline (Visit 2, pre-exposure) to Visit 4 (one week post initiation of dosing). Any shift from normal at baseline to intermediate or Bacterial Vaginosis at Visit 4 will be considered a meaningful change in vaginal flora.

Vaginal microbiome assessment: Samples will be stored frozen for later analysis for the prevalence of microorganisms determined by polymerase chain reaction (PCR) for bacterial ribosomal DNA. The prevalent microorganisms will be compared between the MB66 and placebo arms using Fisher's exact tests, while pre- to post-exposure shifts will be evaluated within each group using McNemar's tests. Prevalence of microorganisms determined by polymerase chain reaction (PCR) for bacterial ribosomal DNA (as the percent of total identified organisms) will be compared between the MB66 and placebo arms using 2 sample t-test if distribution is normal (and after log transformation if not normal). Pre- to post-exposure shifts will be analyzed with a longitudinal mixed model (log transformed if not normally distributed).

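### No within-woman Nugent shift analysis counts a move from intermediate flora to bacterial vaginosis

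*Protocol*

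**What the plan says.** Section 14.4.3 of the protocol (Nugent score) sets three ordered categories: normal 0-3, "Intermediate, 4-6" and "Bacterial Vaginosis, 7-10".

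Section 14.7.4 (Cervicovaginal microbial environment) then plans three uses of the score:

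- A comparison of the categories: "Differences in the categorized Nugent score at each visit and between the MB66 and placebo arms will be evaluated using chi-square tests".
- A McNemar test from Visit 2 (before exposure) to Visit 4 of "pre- to post-exposure shifts between normal (score 0-3) and abnormal (score 4-10) vaginal microflora within each treatment arm".
- A rule for what counts as a change: "Any shift from normal at baseline to intermediate or Bacterial Vaginosis at Visit 4 will be considered a meaningful change in vaginal flora".

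Two other provisions bear on the point. Among vaginal flora conditions, exclusion criterion 19 in section 9.3 names "symptomatic bacterial vaginosis within 14 days of enrollment"; no eligibility criterion uses a Nugent score. Section 12.1.1 grades adverse events by the DAIDS tables, "except that asymptomatic BV will not be considered an AE".

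**The concern.** The protocol separates intermediate flora from BV when it defines the score, then merges the two when it measures change within a woman. A woman who starts at 4, 5 or 6 is already on the abnormal side of the only cut used, so no later deterioration can register as a shift.

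One exploratory objective is to compare the effects of MB66 and placebo film on the vaginal microbial environment, and the Nugent score is named as one of its measures. New BV during product use is a central outcome for that objective. If some new BV is left out of the shift results because of where the woman began, those results are a weaker guide to later studies, which is the use that section 14.7.4 gives them.

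**Working it through.** The protocol states no sample size, power or expected frequency for this endpoint, so there is no figure to reproduce. The check applies the stated rules to all possible scores.

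**1. Apply the rules to individual moves (Visit 2 to Visit 4).**

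| Move | Category change | Meets the change rule | McNemar pair |
|---|---|---|---|
| 3 to 4 | normal to intermediate | yes | discordant |
| 0 to 10 | normal to BV | yes | discordant |
| 6 to 7 | intermediate to BV | no | concordant |
| 4 to 10 | intermediate to BV | no | concordant |

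**2. Count all score pairs that worsen by category.** Scores run from 0 to 10, as the category limits imply: four normal values, three intermediate, four BV.

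- Normal to intermediate: 4 x 3 = 12, all counted.
- Normal to BV: 4 x 4 = 16, all counted.
- Intermediate to BV: 3 x 4 = 12, none counted.

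So 28 of 40 worsening pairs count, and the 12 that do not are all moves from intermediate to BV. These are possible score pairs, not frequencies in patients.

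**3. Can such women be in the trial?** Yes. Symptomatic BV is excluded, an intermediate score is not, and the first scheduled Gram stain is at Visit 2, the day of the first dose (Tables 19 and 20).

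**4. Does adverse event reporting catch the move?** Only if the BV is symptomatic.

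**5. How many women?** Let q be the share of women who are intermediate at baseline. The documents do not give it; q from 5% to 30% is an assumption. With 15 evaluable women per arm in Segment B, the expected number is 15q and the chance of at least one is 1 - (1 - q)^15.

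| q | Expected number of 15 | Chance of at least one |
|---|---|---|
| 5% | 0.75 | 0.54 |
| 10% | 1.5 | 0.79 |
| 20% | 3.0 | 0.97 |
| 30% | 4.5 | 0.995 |

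These are women whose progression to BV could not be counted, not women who would progress. Each woman is 1/15 = 6.7 percentage points of an arm.

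**6. Can the planned comparison between arms see the move?** Take a hypothetical case. Each arm has 11 normal and 4 intermediate women at baseline. All 4 intermediate women on active film move to BV, and the 4 on placebo stay intermediate. The Visit 4 table (normal/intermediate/BV) is 11/0/4 against 11/4/0. The expected count is 11 in each normal cell and 2 in each of the other four cells, so chi-square = 4 x (2^2/2) = 8.0 on 2 degrees of freedom, p = 0.018. With expected counts of 2 the approximation is rough, but the comparison does respond.

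**The case against.** The strongest reply is that flora disturbance is not judged on the Nugent shift alone. Section 14.4.3 defines a pH change (below 4.5 at baseline to 4.5 or above at Visit 4) and a microbiome change (from lactobacillus dominance to dominance by BV-associated bacteria). Section 14.7.4 adds mixed models of pH and of bacterial proportions that do not restrict baseline. The three-category chi-square is a valid randomised comparison at Visit 4, and step 6 shows that it can respond. Normal versus abnormal is also a coherent split, McNemar needs a binary variable, and no decision hangs on the change rule.

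Most of this stands. A reader might infer that new BV in women who start intermediate is invisible to every shift endpoint; the documents do not support that. The cover is only partial, however. The pH and community definitions also need a favourable baseline. The microbiome swabs are taken only in Segment B and are stored for later analysis, with the laboratory still to be determined. The chi-square compares arms at a visit and does not follow each woman from her own starting category.

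Two further inferences should not be drawn. Counting a move from 3 to 4 is not itself a fault: any rule based on categories counts its smallest boundary crossing, including the one proposed below. Nor can it be said that women unable to have the event dilute a result, because the protocol specifies no whole-arm proportion of meaningful change and McNemar uses only discordant pairs.

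**Conclusion.** The point holds in a limited form. Neither the change rule nor the McNemar test counts a move from intermediate flora to BV, which the protocol's own categories treat as a worsening. The gap applies to women who can enrol, and adverse event reporting does not close it when the BV is asymptomatic.

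Severity is minor. The number of women affected is unknown. The average of 0.75 to 4.5 per arm of 15 rests wholly on the assumed 5% to 30% baseline share, and the documents give no rate of progression from which to estimate missed cases. The endpoint is exploratory. The Nugent score plays no part in the primary endpoint or in the pause and stopping criteria of section 13.8, so neither is affected. The change is worth making because it improves a rule the protocol already fixes, at almost no cost.

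**What to change.** In section 14.7.4, and in the SAP to match:

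- Define a meaningful change as any worsening of Nugent category from Visit 2 to Visit 4: normal to intermediate, normal to BV, or intermediate to BV.
- Apply it to women with a baseline score below 7, since those already at 7 or above cannot worsen by category.
- Report new BV (below 7 at Visit 2, 7 or above at Visit 4) as its own line by arm.
- Show the 3x3 table of baseline by Visit 4 category for each arm.
- Keep the McNemar test on 0-3 versus 4-10 as planned.

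Under this definition all 40 worsening score pairs count, against 28 now. The cost is a few lines of text and one extra table. Gram stains are already scheduled at Visits 2 and 4, so no new procedure, sample or participant is needed.

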##### Levels of Immune mediators in Cervicovaginal Lavage

These measures will be compared between groups using two-sample t-tests. Based on previous experience with these outcomes, it is anticipated that log-transformations of the outcome measures will need to be performed prior to performing group comparisons to control for the skewed nature of the data. Pre- to post-exposure shifts will be analyzed after log transformation with a longitudinal mixed model. In addition to these models, adjusted models (i.e. ANCOVA instead of two-sample t-tests) will be considered when comparing groups. These models would include the baseline HSV seropositivity as a covariate in the models.

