| Physical Exam            | Vital signs (temperature, blood pressure, and heart rate)
Physical exam
Height and weight (to be done only at screening)                                                                                                                                                                                                             |

| Component                                                                                                 | Procedure/Analysis                                                                                                                                                                                       |
|-----------------------------------------------------------------------------------------------------------|----------------------------------------------------------------------------------------------------------------------------------------------------------------------------------------------------------|
| Pelvic Exam                                                                                        | Gynecologic exam including visual inspection of external genitalia, speculum, and bimanual exam§
Vaginal swab for pH Δ
Vaginal swab for wet prep Δ
Pap smear Δ |
| CVL                                                                                                | Baseline anti-viral activity, MAb levels, immune mediators                                                                                                                                               |
| Δ If clinically indicated
§ Note the bimanual exam is only required at screening |                                                                                                                                                                                                          |

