### Levels of Immune mediators in Cervicovaginal Lavage

Concentrations of cytokines and other immune mediators will be measured before and after study film exposure.

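### Segment B compares immune mediators and vaginal pH between arms with unadjusted t-tests, forgoing precision available from each outcome's own baseline, which is already collected

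*Protocol*

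**What the plan says.** Protocol section 14.7.4 sets out the exploratory analyses.

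- **Immune mediators.** "These measures will be compared between groups using two-sample t-tests", with log transformation expected because the data are skewed. The text adds that "adjusted models (i.e. ANCOVA instead of two-sample t-tests) will be considered when comparing groups", and the covariate it names is HSV serostatus: "These models would include the baseline HSV seropositivity as a covariate in the models". Separately, "Pre- to post-exposure shifts will be analyzed after log transformation with a longitudinal mixed model".
- **Vaginal pH.** "Vaginal pH levels will be compared between groups using two-sample t-tests". Separately, "Pre- to post-exposure shifts will be analyzed with a longitudinal mixed model". No adjusted comparison between arms is offered.

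Baselines exist for both outcomes. Section 14.4.3 states that "Concentrations of cytokines and other immune mediators will be measured before and after study film exposure". Table 10 lists the Segment B screening lavage as "Baseline anti-viral activity, MAb levels, immune mediators". Table 11 schedules a vaginal pH swab at Visit 2, and section 11.1.2.3 places the pelvic specimens before randomisation and before the first film.

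**The concern.** The comparison of active with placebo film on mediators and on the microbial environment is a stated exploratory objective (section 7.3). Section 14.3 explains that the placebo arm is there to separate effects of the vehicle from effects of the antibodies. In a comparison of about 30 women, the outcome's own pre-treatment value is usually the most informative covariate, and here it costs nothing to obtain. The stated between-arm tests leave it out.

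The protocol already accepts the reason for adjusting. In the antiviral-activity paragraph of section 14.7.4 it justifies ANCOVA by a possible imbalance between groups in a pre-treatment characteristic. That reason applies equally to the baseline mediator level and the baseline pH. Section 14.7.4 also promises effect sizes for all between-film comparisons as guidance for later studies, so the precision of these estimates matters even if few tests are significant.

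**Working it through.** **Inputs.** 15 evaluable women per arm, 1:1 (sections 8.4.2 and 14.7.4). Two-sided alpha 0.05 is stated only for the Fisher comparison in section 14.3 and is assumed here for the t-tests. The correlation rho between an outcome's baseline and follow-up values is not in the protocol; 0.3, 0.5 and 0.7 are assumed. Differences are in units of the between-woman SD (log scale for mediators).

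**Check of the setting.** The protocol gives no power or detectable difference for mediators or pH, so there is no figure of its own to reproduce for this point. Its Table 18 uses the same 15 per arm. Exact enumeration of Fisher's test gives 89.0%, 83.8%, 88.1% and 87.2% against the stated 88%, 83%, 88% and 87%, which agrees closely.

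**Unadjusted t-test.** With 28 degrees of freedom and the noncentral t distribution, the difference detectable with 80% power is 1.06 SD. Power for a true difference of 0.8 SD is 56%.

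**Adjusting for own baseline.** ANCOVA multiplies the residual SD by sqrt(1 − rho²). The detectable difference becomes 1.06 × sqrt(1 − rho²), and the t-test sample size giving equal precision is 15 / (1 − rho²). Power is computed with 27 degrees of freedom.

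| Assumed rho | 1 − rho² | Detectable difference, 80% power | Power for 0.8 SD | Equivalent women per arm |
|---|---|---|---|---|
| none (t-test) | 1 | 1.06 SD | 56% | 15 |
| 0.3 | 0.91 | 1.06 × 0.954 = 1.01 SD | 60% | 16.5 |
| 0.5 | 0.75 | 1.06 × 0.866 = 0.92 SD | 68% | 20 |
| 0.7 | 0.51 | 1.06 × 0.714 = 0.76 SD | 84% | 29.4 |

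A simulation of 4,000 trials per value of rho, with a true difference of 0.8 SD, gave 56–57% for the t-test and 59%, 67% and 82% for ANCOVA. These fall slightly below the table because they include the cost of chance baseline imbalance.

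**Cost of the covariate.** It uses one degree of freedom. If baseline were useless (rho = 0), power for 0.8 SD would go from 56.2% to 56.1%.

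**Chance imbalance.** The standard error of the baseline difference between arms is sqrt(2/15) = 0.365 SD. The chance of an imbalance larger than 0.5 SD in either direction is therefore about 17% for any one outcome (normal approximation). The t-test's error rate already allows for this, but the test does not use the observed imbalance to sharpen the estimate.

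**The case against.** The case against has weight.

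- **No validity problem.** A reader might infer that chance baseline imbalance biases these tests or inflates false positives. It does not: under randomisation the t-test keeps its nominal error rate. This stands, and limits the point to precision.
- **Baseline is not ignored.** A reader might infer that the baselines go unused or that adjusting for them is ruled out. The mixed model of pre- to post-exposure shifts uses them and could carry an arm contrast. Section 14.7.3 describes such models as allowing comparisons between groups, though for secondary endpoints. The mediator paragraph names HSV serostatus without excluding other covariates. What remains is that section 14.7.4 states no arm contrast for the mixed model and makes the t-test the between-group comparison.
- **The correlation may be low.** Section 11.1.2.2 allows screening up to 45 days before enrolment, required abstinence starts only 5 days before Visit 2, and section 9.3 lets women with certain infections at screening enrol after treatment. A screening mediator level may then predict follow-up weakly, and the gain is close to the 0.3 row. The pH baseline is taken on the day of first dosing, so this argument does not touch it.
- **The endpoints are exploratory.** Section 14.7.4 says between-film comparisons are not the primary aim. Safety decisions rest on graded adverse events and examination findings (section 13.8). This stands and keeps severity low.
- **It belongs in the SAP.** Section 14.7.2 defers further detail to an SAP, which is not at hand. The protocol has, however, already named the test and a covariate, so this concerns a stated choice.

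Two further readings go too far. HSV adjustment does not displace baseline adjustment for both outcomes, since the ANCOVA option is not offered for pH. Nor is HSV serostatus necessarily unobtainable: section 6.2.2 notes that endogenous anti-HSV antibodies bind in the ELISA, and baseline serum is scheduled for that assay.

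**Conclusion.** The point holds as a low-severity improvement. The between-arm tests stated for mediators and pH are valid but less precise than an analysis using each outcome's own baseline, and those baselines are already scheduled. The size depends on a correlation the protocol does not give. At 15 per arm, the detectable difference falls from about 1.06 SD to 1.01 SD at rho 0.3, 0.92 SD at 0.5 and 0.76 SD at 0.7. This assumes two-sided 0.05, roughly normal data after any transformation, and complete data on 15 women per arm. The gain for mediators may lie at the low end. Neither the primary safety analysis nor any decision rule is affected.

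**What to change.** In section 14.7.4, or in the SAP with a matching change to that section, make the lead active-placebo comparison in Segment B an ANCOVA adjusted for the outcome's own baseline: the log screening-lavage value for each mediator, and the Visit 2 pre-dose value for pH. Equivalently, state that the already planned mixed model includes arm-by-visit terms, accounts for that baseline, and supplies the arm contrast. Report the adjusted difference for pH and the adjusted ratio for mediators, each with a 95% confidence interval. Keep HSV serostatus as an optional additional covariate for mediators. The unadjusted t-test can stay as a supporting analysis.

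The cost is about two sentences and one degree of freedom per model. No new samples, visits or assays are needed.
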